### Patient and public involvement

To support the translation of the trial’s findings into programs and policies, we will conduct stakeholder engagement workshops in Bangladesh during the trial preparation phase and results dissemination. We will engage different stakeholders from health, housing and construction sectors (Government of Bangladesh, engineering institutes, NGOs in housing and shelters, commercial companies on sustainable construction materials) and stakeholders working in climate change climate adaptation strategies for housing, shelters and water and sanitation. During the first workshop, we will gain input on proposed concrete floor design, health outcome measurement, and planned research outputs from stakeholders. We will also identify the gaps and areas for improvement in current policies, programs, and resources related to housing in rural Bangladesh. In both workshops, we will discuss bottlenecks and potential barriers to scaling up a potential improved flooring intervention and challenges related to sourcing sustainable materials for household floors.

The study team will convene community engagement meetings in each union and upazila in the study site. Attendees will include administrative officials, elected members, religious leaders, and local non-elected leaders. To build trust with the community, the study team will introduce study objectives, discuss potential community benefits, explain the randomisation process and intervention implementation plan, and address any concerns. If community leaders agree, then the team will proceed with recruitment. icddr,b will meet with leaders every 6 months to provide updates on study activities and learn about any other ongoing interventions in the study area.

### Enrollment

Field staff will select a random location in each union using spatial software. If a union spans both sides of the Jamuna river or one of its distributaries, a new random location will be used on each side of the river. The eligible household nearest to the random location will be selected as the first household. Field staff will discuss the trial with adults in the eligible household, including pregnant mothers, and obtain written informed consent (Appendix 1). Field staff will then spin a bottle and move towards the next eligible household in the direction indicated by the top of the bottle. To prevent contamination between households in the intervention and control arms, we will ensure a minimum 100m buffer between study households.

### Baseline survey

The study team will administer a baseline survey to record household construction materials, household census, assets, income, animal ownership, WASH infrastructure and practices, demographics, maternal depression, and the illness and activities of a non-index child aged <3 years (index children will be in utero) (Table 2). Surveys will include questions about satisfaction with housing and floor quality. Field staff will visually assess floors for cracks, damage, cleanliness, and the presence of animal feces, food scraps, or trash. Field staff will record participant names and cell phone numbers to assist with tracking should participants relocate during the follow-up period. Field staff will receive standardized training on survey administration and sample collection.

### Randomisation

The trial will use household-level randomisation stratified by geographic block. This design will ensure that intervention and control groups are evenly distributed across the study area and support baseline balance of participant characteristics between arms. Using a block randomised design is also expected to increase study efficiency by accounting for strong geographic clustering of enteric infection (Arnold et al. 2024). As households are enrolled, they will be formed into geographic blocks of 10 spatially contiguous households. There will be no spatial overlap in geographic blocks. Using R statistical software, a Stanford investigator not involved in the data collection will randomly assign households within each block to control and intervention arms in a 1:1 ratio. A random subsample of 50 intervention households stratified by block will be assigned to receive a green concrete floor. Due to the nature of the intervention, it will not be possible to blind participants to a randomised study arm. Laboratory staff and data analysts will be blinded during primary and secondary outcome analyses of intervention effects.

### Intervention

A local non-governmental organization that is not involved in the research will install concrete floors in 400 intervention households before the birth cohort is born. The control group will receive no interventions. The construction team will remove the top layer of the floor and then create a compacted soil foundation. To increase durability during floods and heavy rainfall, the minimum floor height will be 18 inches. They will retain or change the soil foundation of the home according to the household’s preference. The soil foundation will then be covered with a sand layer followed by a layer of bricks and then cement, followed by sealant. The installation process takes approximately 5 days, and then the floor must cure for approximately 7 days. The entire process takes approximately 14 days, and during this time household members will temporarily relocate, and they will return when curing is complete. If it has rained recently, the field team will wait at least 2 days after it stops raining before installing the concrete floor.

In a subsample of the treatment arm (N=50), we will use an alternative cement mix with fly ash that is likely produced with fewer greenhouse gas emissions than ordinary portland cement. 20% of ordinary portland cement will be replaced with fly ash, and commercially produced “green” blocks will be used instead of traditional bricks as supply availability permits. Green blocks will be made of a mixture of cement, fly ash and recycled aggregates.

### Participant retention

To minimize attrition in the control arm, we will compensate mothers from control households with 500 Bangladeshi Taka ($4.27 USD) after completion of each follow-up survey at 3, 6, 12, 18 and 24 months.

### Follow-up measurements

Field staff will conduct follow-up surveys in all intervention and control households at 3, 6, 12, 18 and 24 months (Table 2). They will conduct household surveys, blood spot and stool collection in the full study sample (N=800). The following potential mediators and outcomes will be measured in subsamples: maternal bandwidth, time use and child cognitive development (N=400), environmental samples (N=400 for STH by qPCR, N=110 for STH larvation detected using microscopy, N=110 for *E. coli*, N=110 for extended-spectrum beta-lactamase producing *E. coli*), video observations (N=60) (Figure 2). When selecting subsamples of households for additional measurements, households will be randomly selected stratified by geographic block and study arm. Additional subsamples will be nested within the largest group. The same subsamples will be used across follow-up rounds for those with repeated measures. If any of the households included in the subsamples are lost to follow-up at a particular measurement, they will be replaced with another block-stratified randomly sampled household from the same study arm.

### Birth survey

Field staff will ask study participants to call them once a mother begins labor and when the index child is born. A survey will be conducted as early as possible after birth (up to four weeks from birth) to record obstetric and birth outcomes. If the mother is temporarily residing away from the study household, field staff will travel to the mother’s location if it is within a study upazila. The birth survey includes questions about antenatal care utilization, delivery location, delivery mode, obstetric complications, gestational age, and neonatal mortality. Field staff will measure weight, length, and head circumference.

### Household surveys

At each follow-up, the field team will administer a survey to mothers of the birth cohort to assess any changes to housing materials, household membership, and household assets (Table 2). Follow-up surveys will collect the same measurements as baseline as well as maternal bandwidth, maternal time use, child motor and cognitive development, child anthropometry and child vaccination status. Additionally, mothers will be asked to report index child illness symptoms and daily activities for the index child.

### Stool collection

At 6, 12, 18, and 24 month follow-ups, field staff will provide caregivers with a sterile container to collect stool from the index child. They will return to pick up the collected stool the following morning and will characterize stool consistency using the modified Bristol Stool Form Scale for children (Lane et al. 2011). Field staff will aliquot 0.5g of stool with 1 mL of Zymo DNA/RNA Shield (Zymo Research, Irvine, California) at the household for stool specimens that will be used for metagenomic sequencing. The samples will be transported on ice to the icddr,b laboratory in Dhaka while maintaining a temperature from 4-10°C. For qPCR analyses, 0.5g stool will be aliquoted with 1 mL 100% ethanol and stored at −80°C prior to qPCR analysis. For antimicrobial resistance analyses, stool will be stored at 4°C with no preservatives prior to analysis within 24 hours of specimen collection. After the final round of stool collection at age 24 months, all household members will be offered deworming medication.

### Blood collection

At 6, 12, 18, and 24 month follow-ups, field staff will collect dried blood spots from the index child. After blood spots are dried for 24 hours, they will be transported to the icddr,b laboratory in Dhaka and archived at −80°C for analyses in future studies.

### Environmental sample collection

At 6, 12, 18, and 24 month follow-ups, field staff will collect dust from floors in a subset of households (N=400). In a smaller subset (N=110), the staff will also collect a floor swab and child hand rinse from index children. To collect dust from floors, staff will use a 0.5 x 0.5 m sterilized metal stencil to mark up to 8 adjacent floor areas (total 2 m^2^), starting next to the head of the bed where the index child usually sleeps. They will sweep the area within the stencil with a sterilized brush once vertically and then once horizontally. They will collect the resulting dust using a sterile scoop and place it in a sterile Whirlpak bag. Staff will then mark an adjacent 0.5 x 0.5 m floor area and swab the area within the stencil with a sterile pre-hydrated sponge once vertically and then once horizontally and place the sponge in a sterile Whirlpak bag. To collect index child hand rinses, staff will ask the caregiver to place child’s hands, one at a time, into a sterile Whirlpak bag pre-filled with 250 mL of sterile water. They will massage each hand for 15 seconds from outside the bag, then shake the Whirlpak bag for 15 seconds with the hand submerged.

At the 6 month follow-up only, field staff will collect additional samples in a subset (N=110). This will provide an early assessment of intervention effectiveness on a wider range of matrices as well as detect additional sources of contamination in the domestic environment. The additional sample types include: drinking water (for index child or other children <5 years), prepared food (for index child or other children <5 years), floor soil (in control arm only), courtyard soil, and cow and chicken feces from animals that stay in the compound. To collect drinking water, field staff will ask the caregiver to bring them a glass of water the same way they would give it to the index child, or to another child <5 years if the index child is not yet drinking water. Staff will pour approximately 250 mL of water from the glass into a sterile Whirlpak bag. To collect prepared food, staff will ask the caregiver to bring them a small portion of food the same way they would give it to the index child, or to another child <5 years if the index child is not yet eating food. Staff will use a 50 mL sterile tube with a sterile spoon to collect approximately 50 g of food. To collect floor soil, field staff will use a sterilized metal stencil to mark an additional 0.5 m x 0.5 m floor area near the child’s sleeping area as described above. They will scrape a 5 mL sterile tube along a horizontal line within the stencil to collect approximately 5 g of sample for sequencing. They will then use a 50 mL sterile tube with a sterile spoon to scrape the remaining area within the stencil once vertically and once horizontally; they will repeat these steps until the tube is full to obtain approximately 50 g of sample to determine moisture content and soil type. To collect courtyard soil, field staff will use a sterilized metal stencil to mark a 0.3 m x 0.3 m area at the entrance to the household where the index child lives and follow the same procedure as floor soil collection. To collect cow and chicken feces, field staff will ask the caregiver to identify feces from recent defecation by their animals, then use a 50 mL sterile tube with a sterile spoon to collect the fecal sample. Zymo DNA/RNA Shield (Zymo Research, Irvine, California) will be added immediately after collection to sample aliquots that will be used for metagenomic sequencing. All samples will be transported on ice to the icddr,b laboratory in Dhaka. Samples that will be used for molecular analyses will immediately be stored at −80°C until DNA extraction. Samples that will be used for culture-based analyses will be stored at 4°C overnight prior to analysis by the next day.

### Laboratory assays

We will test for STH in stool samples and household floor dust samples using quantitative polymerase chain reaction (qPCR) using previously published sequences for the following species which had prevalence >5% in our prior research in rural Bangladesh: *Ascaris lumbricoides*(Pilotte et al. 2019), *Trichuris trichiura*, and *Necator americanus*(Pilotte et al. 2016). DNA will be extracted from stool samples using the QIAamp Fast DNA Stool Mini Kit (51604, QIAGEN GmbH, Hilden, Germany). Extractions will occur following the manufacturer’s suggested protocol with the following changes: (1) Rather than vortexing, homogenization will occur using the Mini-BeadBeater-24 (BioSpec Products). (2) Immediately following homogenization, 1μL of a 100pg/μL stock of an internal recovery and amplification control (IAC) plasmid (Deer, Lampel, and González-Escalona 2010) will be added to each sample. DNA will be extracted from floor dust samples using the DNeasy PowerSoil Pro kit following the manufacturer’s suggested protocol, again with the addition of IAC plasmid. Following DNA extraction, all samples will be tested for the presence of IAC. Amplification of plasmid target will indicate successful recovery of DNA during the extraction procedure and will demonstrate recovered DNA as amplifiable. DNA extracts that fail to produce an IAC result that falls within 3 SD of the mean of all sample IAC results will be eliminated, and the parent sample will undergo re-extraction. Testing for the presence/absence of IAC will occur in accordance with previously published protocols (Papaiakovou et al. 2018).

The presence/absence of STH targets will be determined via the use of previously described small volume, multiparallel qPCR assays. Testing will occur in accordance with published protocols and cycling procedures [60, 61]. Single-well reactions will be used to test all DNA extraction products for the presence of each pathogen of interest, and a qPCR result will be deemed “positive” if testing produces an amplification curve with a Ct value <40.

In a random subsample (N=110) stratified by geographic block, we will determine whether STH ova are larvated using our previously validated method of incubation followed by microscopy since larvated ova can transmit infections to humans, whereas non-larvated ova cannot (Steinbaum et al. 2017).

In the same subsample (N=110), we will use IDEXX Quanti-Tray/2000 with Colilert-24 (IDEXX Laboratories, Westbrooke, Maine) to enumerate the most probable number (MPN) of *E. coli* in floor swab and child hand rinse samples. Swabs will be eluted by adding 100 mL of sterile water to the Whirlpak bag containing the sponge, massaging the swab from outside the bag for 15 seconds, then swirling the Whirlpak bag for 15 seconds. This step will be repeated three times to generate 300 mL of eluate (Harris et al. 2016). 5 mL of the eluate will then be diluted with 95 mL of sterile water to generate a 100 mL aliquot for IDEXX testing. 50 mL of child hand rinse water will be diluted with 50 mL of sterile water to generate a 100 mL aliquot for IDEXX testing. For floor swab samples, a second 100 mL aliquot will be processed after adding 80 μL of filter-sterilized 5 mg/mL cefotaxime solution (final concentration of 4 μg/mL in the 100 mL aliquot) to enumerate the MPN of cefotaxime-resistant *E. coli* (Hornsby et al. 2023).

In the same subsample (N=110), we will also detect and enumerate extended-spectrum beta-lactamase producing *E. coli* (ESBL-E) in the following sample types: child stool, cow and chicken feces from the same compound, floor swab, courtyard soil, child hand rinse, drinking water, and prepared food. We will use CHROMagarTM ESBL media to isolate and identify ESBL-E (Hossain et al. 2021). Selected colonies from each plate will be analyzed by qPCR for major ESBL genes (CTX-M, SHV, TEM, OXA) following previously published protocols (Mahmud et al. 2022). Isolates from previous studies will be used as positive controls. For selected isolates, antibiotic susceptibility will be determined using the Kirby-Bauer disk diffusion method following guidelines of the Clinical and Laboratory Standards Institute (CLSI) and European Committee on Antimicrobial Susceptibility Testing (EUCAST) (“CLSI Publishes M100—Performance Standards for Antimicrobial Susceptibility Testing, 32nd Edition,” n.d., “Breakpoint Tables for Interpretation of MICs and Zone Diameters” 2021).

In the same subsample (N=110), we will perform metagenomic sequencing of child stool, floor soil, cow feces and chicken feces samples from each follow-up round. Floor soil will only be collected from control arm households (N=55) because we expect that the quantity of soil needed for DNA extraction (10 g) will not be available on concrete floors. We will combine 10 fecal samples of each type and 5 floor soil samples to generate 11 composite samples of each type. We will extract DNA from each composite sample using DNeasy PowerMax Soil Kits for soil samples and Qiagen QIAamp PowerFecal Pro DNA Kits for stool samples. Metagenomic shotgun sequencing will be performed using the Illumina platform. We will use Kraken2 (Wood, Lu, and Langmead 2019) to perform taxonomic classification of reads to identify pathogens and bacterial antimicrobial resistance genes in each sample.

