## Introduction

The United Nations has enshrined basic housing as a human right, and housing improvements are associated with improved health (Thomson et al. 2009; Thomson, Sellstrom, and Petticrew 2013). Yet, 58.8% of homes in low-income countries are unimproved, with soil floors and walls (Morakinyo, Fagbamigbe, and Adebowale 2022) made of palm or thatch, and few studies have investigated health benefits of housing upgrades in low- or middle-income countries (LMICs). In low-income homes, inadequate sanitation infrastructure can result in contamination of household soil and surfaces with human and animal feces. In particular, soil floors are a reservoir for enteric pathogens such as soil-transmitted helminths (STH), *Shigella*, and pathogenic *E. coli* (Steinbaum et al. 2019, 2016; Shrivastava et al. 2020). Multiple studies have found that the amount of *E. coli* and STH is similar or higher on soil floors inside the home than on latrine floors (Steinbaum et al. 2016; Pickering et al. 2012; Schulz and Kroeger 1992). *Ascaris lumbricoides* eggs are extremely hardy and can survive for years in soil; other STH species can survive for weeks or months (S. Brooker, Clements, and Bundy 2006; Ransom and Foster 1920). Soil is also a reservoir of antimicrobial resistant pathogens because microorganisms in soil can exchange genes with those in feces deposited on soil (Zhu et al. 2019). Children frequently play, eat, and drink on floors that are contaminated with human or animal feces, and young children frequently ingest soil, increasing their risk of infection with STH, other enteric pathogens, and antimicrobial resistant pathogens (Kwong, Ercumen, Pickering, Arsenault, et al. 2020; Kwong, Ercumen, Pickering, Unicomb, et al. 2020; Goddard et al. 2020; Ercumen, Pickering, et al. 2018; Ercumen, Mertens, et al. 2018; Fuhrmeister et al. 2020; Pickering, Swarthout, et al. 2019; Kwong et al. 2021).

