### Outcomes

Our primary outcome is the prevalence of any of the following STH infections, *Ascaris lumbricoides, Necator americanus, or Trichuris trichiura*, detected using qPCR in child stool at 6, 12, 18, or 24 months after the birth of the index child. Secondary outcomes include the prevalence of each STH species by qPCR at child ages 6, 12, 18, or 24 months and caregiver-reported diarrhea in the past 7 days and diarrhea confirmed using stool consistency (Lane et al. 2011) at each follow-up. Additional secondary outcomes are listed in Table 1.

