### Cost-effectiveness analysis

We will conduct cost-effectiveness to examine both the costs and health outcomes of the concrete floor intervention. We will collect data on floor installation costs from a program perspective, separating material and labor costs, since in the future households may install floors themselves. Using an ingredients-based approach, we will record costs for individual line items within categories including capital costs, materials, transportation, personnel, and operations. We will then adapt our previously published natural history and cost-effectiveness models of childhood helminth infections and enteric fever to project the health impacts and cost-effectiveness of floor installation (Lo et al. 2016, 2018; Ryckman et al. 2021; Weyant et al. 2024). We will populate the model with outcome rates from the control and intervention arms of this trial, simulate age-specific risk over a ten-year period, and project DALYs for each health outcome for households with concrete floors and soil floors.

We will calculate DALYs for child STH infections, child diarrhea, child wasting, and maternal depression using published disability weights (Global Burden of Disease Collaborative Network/Institute for Health Metrics and Evaluation, n.d.). While we expect the intervention to influence a broad range of outcomes, disability weights are only available for the subset listed above. We will calculate disability weights for hookworm-associated anemia as the product of the disability weight for anemia due to hookworm disease by the probability that an individual infected with hookworm develops anemia (Bartsch et al. 2016). For each STH infection, we will estimate the probability of mild, moderate, and severe infections based on Ct values from qPCR using data from a prior study of children in rural Bangladesh (Benjamin-Chung et al. 2020). For diarrhea, we will calculate weights assuming the distribution of mild, moderate, and severe diarrhea is the same as found in the MAL-ED study in Bangladesh (Platts-Mills et al. 2015).

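### The primary outcome scores any stool DNA below Ct 40 in one well as infection, so swallowed soil may add positives, more often in the control arm; the size is unknown

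*Protocol article*

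**What the plan says.** In the Outcomes section the primary outcome is the prevalence of infection with any of three species, "detected using qPCR in child stool at 6, 12, 18, or 24 months after the birth of the index child". Laboratory assays fixes how a stool becomes positive: "Single-well reactions will be used to test all DNA extraction products for the presence of each pathogen of interest", and a result is positive if "testing produces an amplification curve with a Ct value <40". The article states no repeat-well rule and no second threshold for stool. The internal control plasmid checks that DNA was recovered and can be amplified.

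Other sections bear on where such DNA could come from:

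- The Introduction calls soil floors a reservoir for these worms and says that "young children frequently ingest soil".
- Laboratory assays applies qPCR for the same species to household floor dust, and says that only larvated ova can transmit infection.
- The Introduction's account of mechanisms says concrete takes away most of the soil inside the home. Statistical analysis adds that, in pilot data, concrete floors in 40% of households may give too little dust to extract.
- Table 1 lists egg counts in child stool by Kato-Katz as a secondary outcome.
- Cost-effectiveness analysis already treats Ct as informative: "we will estimate the probability of mild, moderate, and severe infections based on Ct values from qPCR".

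**The concern.** The outcome is named infection, but what is measured is the presence of DNA. A child who swallows soil containing ova may pass detectable DNA without being infected. On the protocol's own reasoning, swallowed ova that have not larvated cannot infect, yet their DNA would still meet the positivity rule.

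Misclassification of this kind would not be balanced between arms, because the intervention acts on its source. With less indoor soil there would be fewer soil-derived positives in the intervention arm, and the prevalence ratio would move towards benefit for a reason other than fewer infections. Blinding the laboratory does not help, since the DNA is in the sample before it arrives. The internal control guards against failed extraction or inhibition, that is, against false negatives. At stake is whether a ratio below 1 can be read as infections prevented, in a trial meant to inform policy on floor installation.

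**Working it through.** **What the plan gives.** The article has no figure for this bias, so there is none to reproduce. The nearest one, 336 households per arm, does not follow from the stated inputs with four rounds: 615 per arm for one measurement × (1 + 3 × 0.066)/4 = 184. That is a separate matter. Here the sample size serves only to set precision.

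**Inputs from Sample size calculation.** Control prevalence 20%, design prevalence ratio 0.70 (so 14% in the intervention arm), four rounds, intraclass correlation (ICC) 0.066, two-sided 5% test, and 400 per arm with 15% loss, so 400 × 0.85 = 340. As a second case I use an ICC of 0.40, because four rounds would give about 336 per arm only with an ICC of roughly 0.38 to 0.40.

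**Assumption, not in the documents.** A net share f of uninfected control stools tests positive from swallowed soil, over and above the intervention arm. I take f from 1% to 5%.

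**Formulas.**
- Observed control prevalence = 0.20 + 0.80f.
- Apparent ratio with no true effect = 0.20/(0.20 + 0.80f).
- Apparent ratio with a true ratio of 0.70 = 0.14/(0.20 + 0.80f).
- Effective n per arm = 340 × 4/(1 + 3 × ICC), which is 1,135 at ICC 0.066 and 618 at ICC 0.40.
- SE of the log ratio = √(2 × (0.80/0.20)/effective n), which is 0.084 and 0.114.
- Chance of a significant result = P(|Z + ln(ratio)/SE| > 1.96).

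| f | Observed control | Apparent ratio, truth 1 | Significant, ICC 0.066 | Significant, ICC 0.40 | Apparent ratio, truth 0.70 |
|---|---|---|---|---|---|
| 1% | 20.8% | 0.96 | 8% | 6% | 0.67 |
| 2% | 21.6% | 0.93 | 15% | 10% | 0.65 |
| 3% | 22.4% | 0.89 | 27% | 17% | 0.63 |
| 5% | 24.0% | 0.83 | 58% | 36% | 0.58 |

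The SE is taken at 20% in both arms. Using 24% in the control arm moves the 58% to about 63%. Conditioning on block is ignored.

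**How much soil DNA this implies.** The artefact's share of control positives is 0.80f/(0.20 + 0.80f): 0.8/20.8 = 3.8% at f = 1%, and 4/24 = 16.7% at f = 5%.

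**Cross-check in another form.** Hold observed control prevalence at 20% and let a net share s of those positives be soil DNA that the floor removes. With no infection prevented, the ratio is 1 − s. At 336 per arm, s = 0.05 gives 0.95 with a 9% chance of significance, and s = 0.10 gives 0.90 with 23%. The two forms agree.

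**Direction.** Let a share q of control positives be soil DNA and let the floor remove a fraction r of them. The apparent ratio is then (1 − q) × true ratio + q × (1 − r). With a true ratio of 1, any r above 0 gives a value below 1. With a true ratio of 0.70 and q = 0.10, the result is 0.63 if all soil positives are removed and 0.73 if none are. Bias towards benefit therefore needs the floor to cut soil positives by a larger fraction than it cuts infections.

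**The case against.** The strongest reply is that nothing in the article says how often swallowed soil makes a stool positive. The Introduction presents soil ingestion as a route to infection, not as a source of false positives, and the statement about larvated ova concerns infectivity, not stool results. That stands: the mechanism follows from the protocol's premises, but its size does not.

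A second reply is that a check is already planned. Kato-Katz egg counts do not depend on trace DNA or on a Ct cut-off. This stands in part. They are a secondary outcome, are not described under Stool collection or Laboratory assays, are not tied to the primary claim, and could also count swallowed eggs.

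A third is that Ct sensitivity analyses belong in the analysis plan, which is not shown. That is fair, and their absence from the article is not the criticism. The positivity rule is fixed in the article, and the proposal is a guard on how its result is read. If the analysis plan already contains such an analysis, the point is met.

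A reader might also infer more than the text supports:

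- That stools pick up soil from the floor on their way into the container. The article says only that "field staff will provide caregivers with a sterile container to collect stool from the index child" and does not describe where the stool is passed.
- That Ct <40 is unusually permissive. The article ranks it against nothing and refers to published procedures that are not at hand.
- That concrete removes the source altogether. The article says most of the indoor soil, courtyard soil remains in both arms, and the pilot figure leaves about 60% of concrete-floor homes with extractable dust.

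**Conclusion.** The concern holds as a possible differential misclassification of the primary outcome, not as a demonstrated bias. The protocol's own premises give a source of non-infection DNA, a route into the child, and an intervention that reduces the source. With no true effect, the direction is towards benefit.

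The size rests wholly on an assumed f. Over 1% to 5%, a true ratio of 1 appears as 0.96 to 0.83, with a chance of a significant result between 8% and about 60% at the stated ICC. At or below about 1% the effect is minor. The larger figures need about one control positive in six to be artefact, and nothing in the article supports or excludes that. A reader might infer that a ratio of 0.70 could arise with no infection prevented. Arithmetically that needs a net 30% of control positives to be removable soil DNA, for which the article offers no evidence.

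The point merits action because the check is cheap and bears directly on what a positive result would mean.

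**What to change.** 1. Keep Ct <40 as the primary rule.
2. Before unblinding, pre-specify a sensitivity analysis of the primary prevalence ratio at one stricter Ct cut-off per species, and compare Ct distributions among positives by arm.
3. Report both beside the Kato-Katz result wherever the effect is interpreted as fewer infections. An excess of late-Ct positives in the control arm, with a ratio that moves towards 1 at the stricter cut-off, would call for caution in that wording.
4. Optionally, give caregivers in both arms a clean collection sheet and record the surface on which the stool was passed, for description only. Stools should not be excluded for ground contact: that is a post-randomisation variable likely to differ by arm, so exclusion could itself cause selection bias, and it would do nothing about swallowed soil.

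**Cost.** A few lines in the analysis plan and no extra assay, since the Ct values are already needed for the cost-effectiveness model. The optional step adds one form item and up to 800 × 4 = 3,200 sheets.

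**Downside.** A stricter cut-off loses some light true infections, and if floors lower infection intensity the ratio may shift for a genuine reason. It should therefore remain a sensitivity analysis and not replace the primary one.
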